# Single-session intervention on growth mindset on negative emotions for university student mental health (U-SIGMA): a protocol of two-armed randomized controlled trial

**DOI:** 10.1186/s13063-023-07748-5

**Published:** 2023-11-08

**Keywords:** Belief in change, University students, Common mental health symptoms, Help-seeking

## Abstract

**Background:**

The university years are a developmentally crucial phase and a peak period for the onset of mental disorders. The beliefs about the changeability of negative emotion may play an important role in help-seeking. The brief digital growth mindset intervention is potentially scalable and acceptable to enhance adaptive coping and help-seeking for mental health needs in university students. We adapted the Single-session Intervention on Growth Mindset for adolescents (SIGMA) to be applied in university students (U-SIGMA). This protocol introduces a two-armed waitlist randomized controlled trial study to examine the effectiveness and acceptability of U-SIGMA in promoting help-seeking among university students in the Greater Bay Area.

**Methods:**

University students (*N* = 250, ages 18–25) from universities in the Greater Bay Area will be randomized to either the brief digital growth mindset intervention group or the waitlist control group. Participants will report on the mindsets of negative emotions, perceived control over anxiety, attitude toward help-seeking, physical activity, hopelessness, psychological well-being, depression, anxiety, and perceived stress at baseline and the 2-week and 8-week follow-ups through web-based surveys. A 30-min digital intervention will be implemented in the intervention group, with a pre- and post-intervention survey collecting intervention feedback, while the control group will receive the link for intervention after 8 weeks.

**Discussion:**

This protocol introduces the implementation plan of U-SIMGA in multi-cities of the Greater Bay Area. The findings are expected to help provide pioneer evidence for the effectiveness and acceptability of the brief digital intervention for university students in the Chinese context and beyond and contribute to the development of accessible and effective prevention and early intervention for university students’ mental health.

**Trial registration:**

HKU Clinical Trials Registry: HKUCTR-3012; Registered 14 April 2023. http://www.hkuctr.com/Study/Show/7a3ffbc0e03f4d1eac0525450fc5187e.

**Supplementary Information:**

The online version contains supplementary material available at 10.1186/s13063-023-07748-5.

## Background

University students are vulnerable to developing mental health problems. Anxiety and depression are common among university students, with a 12-month prevalence for generalized anxiety disorder and major depressive episodes being 16.7% and 18.5%, respectively [1]. Suffering from mental health symptoms can profoundly affect university students’ work capacity, academic performance, physical health, and graduation rates, impairing their daily functioning [2, 3]. Therefore, developing effective prevention and early intervention for mental disorders in university students is paramountly needed.

Despite the availability of counseling centers in universities, the majority of anxious and depressed students do not actively seek campus-based interventions, partially due to the concerns of stigma and discrimination [4]. Moreover, even for youths who use health care services, the overall number of visits is just 3.9 on average implying a lack of sustained involvement in therapy [5]. Given the large number of students with mental health care needs and the low engagement in traditional services, there is clearly a need to develop briefer, more scalable, non-stigmatizing, and youth-friendly interventions to promote mental health and help-seeking of university students.

Self-guided brief digital psychoeducation interventions are novel initiatives that are potentially scalable and acceptable to help this important segment of population during a critical life course stage [6]. Digital and web-based interventions are easily adopted by young people, provide more anonymity, and enable remote use when it is not possible for students to access conventional face-to-face psychotherapy [7]. Although extant studies on digital intervention have yielded promising results [8, 9], only a limited number of interventions were designed based on the university students’ needs [10]. Brief digital intervention can prompt changes if the design of the intervention is relevant to meaning-making and social context [11].

Growth mindsets, the beliefs in change of personal attributes, are closely related to psychopathology [12], and the mindset intervention has recently been applied to clinical practice [13]. Fixed mindsets are linked to more suppressive emotion regulation and medication therapy choice while growth mindsets are associated with cognitive reappraisal and effort-taking therapy choices, such as counseling [14, 15]. In addition, growth mindsets alleviate the associations between stressful life events and mental distress [16]. The growth mindset interventions have shown promising effects [13, 17], particularly in enhancing perceived emotional control and decreasing anxiety symptoms [18]. However, single-session growth mindset intervention is far from sophisticated and needs further refinement and delicate design for the targeted population. Furthermore, as the effects of single-session intervention may wane over time, booster messages should be adopted to strengthen the efficacy [19]. The current study is to tailor-design a brief digital growth mindset intervention for Hong Kong and mainland Chinese university students based on the extant research findings, including those from overseas and local empirical research.

Previous studies have found that the mindset regarding negative emotions is a key predictor for self-harm, suicidality, social withdrawal [20], gaming disorder [21], depression, and anxiety [22, 23]. Mindsets were also found to mediate the association between depression and suicidality, that is, individuals suffering from depression are less likely to develop suicidal ideation if they have higher growth mindsets [24]. Besides, growth mindsets predict adaptive emotion regulation (e.g., sports) and higher subjective well-being of individuals under adversities [25]. These findings provide strong empirical support that fostering belief-in-change of negative emotions is likely to promote mental health among university students. Based on the findings from these studies, a *S*ingle-session *I*ntervention of *G*rowth *M*indset for *A*dolescents (SIGMA) was designed to examine its effectiveness among secondary school students [26].

Building on our previous research, we have adapted the SIGMA growth mindset intervention and developed a brief digital intervention with boosters for university students, i.e., the U-SIMGA. We included examples relevant to university life and adapted the engaging exercise in the U-SIMGA to match the cognitive ability with university students. This proposed study will conduct a randomized controlled examination on the acceptability and effectiveness of the intervention compared to a waitlist control. University students in Hong Kong and other cities in the Greater Bay Area of Mainland China (mainly from Guangzhou, Shenzhen, and Zhaoqing) are invited to join the study as many universities located in this area and the widespread use of digital devices among university students. The proposed study aims to examine the effectiveness and acceptability of the brief digital growth mindset intervention in promoting university students’ mental health, specifically in [1] enhancing the perceived emotional control, help-seeking intention, psychological well-being, and physical activity and [2] reducing symptoms of anxiety, depression, and stress, and hopelessness. Through the study, we will collect empirical evidence and feedback on the acceptability and effectiveness of single-session interventions for Chinese university students. Based on the findings, further improvement can be made to promote effective and scalable brief digital intervention for university students’ mental health.

### Objectives

The primary objective is to evaluate the effectiveness of a brief digital intervention of growth mindsets on negative emotions in the primary outcome (enhancing perceived control over anxiety) and secondary outcomes (i.e., enhancing attitude toward help-seeking, psychological well-being, and physical activity, and reducing depression, anxiety, stress, and hopelessness) in university students. The secondary objective is to evaluate the acceptability of the brief digital intervention by intervention feedback measures among university students in the Greater Bay Area.

### Hypotheses

We hypothesize that the brief digital growth mindset intervention is effective in the primary outcome of (i) enhancing perceived control over anxiety and secondary outcomes of (ii) increasing attitude toward help-seeking, (iii) reducing hopelessness, (iv) enhancing psychological well-being, (v) increasing physical activities, and (vi) reducing depressive, anxiety, and stress symptoms. Moreover, the effectiveness is hypothesized to be greater among participants with higher anxiety and depression symptom, or higher motivation at changing current emotional status and emotion coping than among those with low or no symptoms or motivation.

## Methods

### Study design

For this randomized controlled trial study, invitations for participation will be sent to the teachers of six universities in the Greater Bay Area, and then they will be asked to forward the invitation to WhatsApp or WeChat student groups. We also recruit through mass email and promotion posters. Students who click on the research link will be invited to read the research information sheet and sign the consent form, and the survey will immediately end for those students who do not agree to participate in the study without signing the consent. *Qualtrics* in Cantonese and *WenJuanXing* survey tool in Mandarin will be used for Hong Kong students and Mainland students respectively. Participants will be randomized into the intervention group or the waitlist control group by adding a “Randomizer” block into the survey flow of two online survey platforms. The expected allocation ratio and concealment can be ensured since the “Randomizer” block will only appear after the baseline assessments have been completed by the participants and conduct the allocation based on a predetermined ratio. Participants assigned to the intervention group will start the intervention instantly, and those in the control group will receive the intervention link after 8 weeks. Three repeated assessments of the measures will be conducted for two groups simultaneously at (i) baseline, (ii) 2-week post-intervention, and (iii) 8-week post-intervention via survey systems *Qualtrics* (for Hong Kong students) and *WenJuanXing* (for mainland students). The design of 2-week and 8-week post-tests is based on the extant studies on single-session or brief intervention [12, 27]. Invitations for follow-up surveys will be sent to the participants who complete the survey at baseline. Each participant will receive incentives (e-voucher or online red packet) with approximate values of US $5 and US $8 when completing the 2-week and 8-week follow-up questionnaires respectively. Thus, the total compensation for participation is US $13. Incentives will be sent to the participants automatically through the online system excluding invalid responses after the screening. The study flow is seen in Fig. 1.

**Fig. 1 Fig1:**
[figure not shown]
CONSORT diagram reflecting the flow of participants through the current study

### Sample size

The sample size was calculated based on a small-to-medium effect size of *Cohen’s d* = *0.40* from prior research [28], power of 0.80, and alpha of 0.05 (two-tailed). It shows a total of 200 participants (100 per arm) are needed. Referring to the attrition rate of around 20% in our previous school-based studies, it is safe to include 250 participants for this study (125 per arm).

### Participant eligibility

Eligible participants are university students (years 1 to 4) from six universities recruited through cluster randomized sampling. The inclusion criteria are as follows: [1] age 18–25; [2] Chinese students with the ability of reading and writing Chinese; [3] enough visual and auditory abilities; and [4] giving consent for participation. Exclusion criteria include the following: [1] no consent; [2] unable to stay focused for at least 45 min for completion of the intervention and survey; [3] intellectual disabled, suffering from severe illness or pain which could result in biased physical or mental health situation of students.

### Brief digital growth mindset intervention and waitlist control group

The randomized controlled trial is designed to demonstrate the superiority of the intervention group to the waitlist group with a 1:1 allocation. The intervention is a web-based intervention, which is adapted from the single-session growth mindset intervention (SIGMA) for secondary school students developed by Zhu et al. [26]. The current intervention adapted the SIGMA intervention content for university students (U-SIGMA) and incorporated boosters to strengthen the effectiveness of the intervention. The U-SIGMA contains five components: (a) introduction of emotional brain to communicate scientific knowledge on emotion and growth mindset regarding emotion, (b) stories and testimonials from university students describing how growth mindsets or fixed mindsets affect their coping with mental health symptoms, (c) emotion coping strategies, (d) common misconceptions and doubts of growth mindset, and (e) self-persuasion writing exercises for participants to share notes on the negative emotion growth mindset with others. Boosters with key messages of intervention are made through e-posters, which will be sent to all participants in the intervention group as reminders weekly from the second week after the intervention through email, WhatsApp, or WeChat, with a total of four times. Besides, boosters will be designed based on the “saying is believing” mechanism, empowering and encouraging the participants to share what they learned with others for knowledge reflection and application. For example, several blanks will be left for the participants to critically think about and write down their own emotional coping strategies or others’ examples of growth mindset based on daily observation. Participants in the waitlist control group will not receive the intervention program until 8 weeks later, though they will be asked to complete three repeated measures at the same time as the intervention group. Figure 2 presents the Standard Protocol Items: Recommendations for Interventional Trial (SPIRIT checklist) about the schedule of enrolment, interventions, and assessments.

**Fig. 2 Fig2:**
[figure not shown]
Schedule of enrolment, intervention, and assessments

### Implementation strategies

Three strategies are adopted to ensure the comprehensibility, relevance, acceptability, and effectiveness of the self-developed digital intervention. First, we formed an advisory group with two undergraduate students and four graduate students, collecting challenges in universities, testimonials of mindsets, personal understandings about growth mindset, and emotion regulation from the perspective of the target population. It is crucial to continuously reflect on the feedback and suggestions in the trial to ensure the contents of the intervention are context-adaptive, self-relevant, and easily understood for university students. We also interviewed them about the duration, type, and flow of the intervention for further improvement in the setting, making sure the intervention is acceptable for the target population. Second, the study will provide opportunities for participants to understand their personal emotional status by immediately providing a system-generated emotion evaluation report based on their responses, which may enhance the motivation for participation and make them feel more self-relevant. Third, the “saying is believing” mechanism is applied throughout the study. Besides the self-persuasion writing exercises that allow the participants to act as “helpers” to others, they are also encouraged to advocate what they have learned and share the intervention link with other university students in need. Participants will receive four digital poster cards designed with key intervention messages and they will be invited to share the cards to other people.

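### Intervention participants are encouraged to share the link and key-message cards before week 8, and no safeguard against control exposure is described, so the effect may be diluted and power may fall below 80%

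*Protocol article*

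**What the plan says.** Four parts of the protocol article bear on this.

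- **Control condition.** Under the heading on the intervention and waitlist group: "Participants in the waitlist control group will not receive the intervention program until 8 weeks later". Study design agrees that "those in the control group will receive the intervention link after 8 weeks".
- **Sharing.** Implementation strategies says of participants that "they are also encouraged to advocate what they have learned and share the intervention link with other university students in need". They also receive four digital cards with the key messages and are invited to pass them on. The self-persuasion mechanism behind this is said to run through the whole study. The intervention section adds four weekly boosters starting in the second week, designed to encourage participants to tell others what they learned.
- **Recruitment and allocation.** Teachers at six universities are asked to "forward the invitation to WhatsApp or WeChat student groups"; mass email and posters are used as well. A randomizer block in each online survey then allocates participants after baseline.
- **Sample size.** Cohen's d is 0.40, with 80% power and two-sided alpha of 0.05: "It shows a total of 200 participants (100 per arm) are needed". Enrolment is set at 250 for attrition of about 20%.

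**The concern.** The control arm is defined by not having the programme before week 8, while the treated arm is given both a reason and a means to pass the programme or its messages to other students. If individuals are randomized, controls sit in the same universities, and partly in the same chat groups, as treated students. The boosters arrive by email, WhatsApp or WeChat, so forwarding is easy.

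A control who sees the module or the cards before the 8-week survey is analysed, correctly under intention to treat, as a control. The contrast then shrinks toward zero. This does not raise the false-positive rate. It lowers power and understates the effect of the programme against no programme. A null result would be hard to interpret, because the planned measures include no question on whether a control had seen the material.

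**Working it through.** **Timing.** Boosters weekly from the second week, four in all, fall at about weeks 2, 3, 4 and 5. All precede the 8-week assessment. They can hardly affect the 2-week assessment, but the article does not hold back link sharing until any particular week.

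**The plan's own figure.** By the normal approximation, n per arm = 2(1.960 + 0.842)²/d² = 15.70/0.16 = 98.1, so 99 per arm. The t-test solution is 99.08, so 100 per arm and 200 in total. Allowing for attrition, 200/0.80 = 250. The stated 200 and 250 reproduce. Power at 100 per arm is 80.4% by t-test (80.7% by normal approximation), so there is no reserve.

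**Dilution.** Let c be the share of controls exposed before assessment and f the fraction of the full effect they obtain. The expected contrast is d(1 − cf) = 0.40(1 − cf). Neither c nor f is in the documents; both are assumptions. The small extra variance in a mixed control arm is ignored. Two-sided t-test power at 100 per arm:

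| c | contrast, f = 1 | power, f = 1 | contrast, f = 0.5 | power, f = 0.5 |
|---|---|---|---|---|
| 0% | 0.40 | 80.4% | 0.40 | 80.4% |
| 5% | 0.38 | 76.2% | 0.39 | 78.4% |
| 10% | 0.36 | 71.7% | 0.38 | 76.2% |
| 20% | 0.32 | 61.5% | 0.36 | 71.7% |
| 30% | 0.28 | 50.4% | 0.34 | 66.7% |

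**Sample size needed to restore 80% power, f = 1** (15.70/d², rounded up per arm, doubled, then divided by 0.80):

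- c = 5%: 109 per arm, 218 evaluable, 273 enrolled
- c = 10%: 122 per arm, 244 evaluable, 305 enrolled
- c = 20%: 154 per arm, 308 evaluable, 385 enrolled

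**Reading the scale.** With 125 controls enrolled, c = 20% means 25 controls exposed and c = 5% means about 6. The f = 1 column is the worst case for a given c; cards alone would be expected to dilute less than the full module.

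**The case against.** Several points on the other side have force.

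- **The link may not open the module.** A reader might infer that anyone holding the shared link can take the programme directly. The article does not say so. Students enter through a research link that leads to consent, baseline and randomization, and a shared link could lead back there. This stands: direct access is a possibility, not a stated fact. It does not remove the point, because the article uses the same term for what controls are sent after week 8, describes no gate, and the cards carry the messages without any link.
- **Exposure would not go wholly unseen.** The scale for mindsets of negative emotions is measured in both arms at all three times and serves as a fidelity check. Improvement among controls would be an indirect signal. It would not identify who was exposed, or separate exposure from other change.
- **Controls may be few among the recipients.** Sharing is aimed at students in need and at people generally, and 125 controls over six universities may be a small part of any participant's contacts. This stands, and is why the table starts at zero.
- **Late responders.** A reader might also infer that controls who answer late get the link before their 8-week survey. The order of survey and link release may be shown in the flow and schedule figures, which were not available here, so the documents do not support that claim.
- **Clusters.** Participant eligibility refers to cluster randomized sampling, and Data analyses says cluster randomization is used. Allocation by university would reduce sharing across arms. The only allocation mechanism described, however, works on individuals.
- **Sharing is part of the intervention.** Correct, and the fix has to respect it.

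**Conclusion.** The concern holds in a limited form. As written, the plan encourages sharing of the link and key messages before the 8-week assessment, draws both arms from shared channels, and describes neither a safeguard nor a direct measure of exposure. Some controls may therefore be exposed, which would bias the contrast toward zero.

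The size is unknown. With full effect in exposed controls, power is about 76% at 5% exposed and 50% at 30%. With half the effect it is about 78% and 67%. Any exposure that has an effect takes power below its uncontaminated value of 80.4%, and all but trivial exposure takes it below the stated 80%. The documents do not show that controls will be treated, nor how many. This is a cheap improvement to the design, not a fatal flaw, and it rests on individual allocation as described in Study design.

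**What to change.** 1. During the trial, use participant-specific or single-use intervention links, or route any shared link through consent and randomization.
2. Word the sharing prompts so that the link and cards are not passed to fellow students at the participating universities until follow-up closes. Keep the writing exercise inside the module as it is.
3. Add one question to the 2-week and 8-week surveys on whether the participant has seen the programme or its cards, and use the answer among controls in a sensitivity analysis beside the intention-to-treat result.
4. Reconcile the references to cluster sampling and cluster randomization in Participant eligibility and Data analyses with the individual randomizer in Study design.

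The cost is a link setting, one survey item at each follow-up and revised wording. The real downside is that part of the peer-sharing component is postponed, so the programme under test changes slightly. Items 1 and 3 alone leave its content unchanged. Where follow-up has already closed, what remains is to report the sharing prompts as a limitation and to examine mindset change among controls as an indirect check.
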